### Objectives and hypothesis

This study was designed to assess whether the psychosocial assessment in patients with HGG can be improved by face-to-face assessment during doctor–patient consultation.

The following aims are addressed:
First, we compare the percentage of HGG patients in distress receiving adequate psychosocial careSecond, we compare the percentage of HGG patients correctly identified as distressed in the two trial arms

We hypothesize that more patients will be adequately assessed regarding distress during the doctor–patient consultation (intervention arm) than by the questionnaire assessment (CAU arm). We further hypothesize that HGG patients assessed in the intervention arm will more frequently receive support than the others. The PICO scheme for this trial is as follows:
Patients: Patients with high-grade gliomaIntervention: Assessment of distress in doctor–patient consultationComparison: Assessment of distress via questionnaireOutcome: Proportion of patients with high levels of distress who receive psychosocial care by specialized services

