#### Conditions of the intervention arm

Psychosocial distress is measured by three questions that emerged as important in a preliminary study. The three questions are:
Has your mood worsened due to the disease?Do physical changes due to the disease, such as numbness, weakness, or feeling exhausted more quickly, put a strain on you?Has your mental capacity worsened as a result of the disease, making it harder for you to concentrate or remember things, for example?

On the basis of the patient’s answers, the doctor offers psychosocial care, if indicated and desired by the patient, and refers the patient to the appropriate specialist services, e.g., psycho-oncological service, clinic social service, outpatient cancer counseling centers, physiotherapy, established psychotherapists, etc.

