### Instruments applied in the study

#### Before the doctor–patient consultation, t1

First patients complete a baseline questionnaire (t1) assessing use of and wish for psychosocial support using an adapted version of a self-developed questionnaire [17]. Further, the European Organization of Research and Treatment of Cancer Core Questionnaire (EORTC QLQ-C30) with its brain module (BN20) will be applied. It is a self-assessment tool to evaluate cancer patients’ quality of life. Validity and reliability have been previously tested in several clinical studies [18].

Patients in the control group complete additionally the DT. This is a self-reporting screening instrument, measuring psychosocial distress by a numerical rating scale accompanied by a 40-item list with problems from different areas of life, e.g., practical, family, emotional problems, etc. [5, 19].

Afterwards, the patients have the doctor–patient consultation. In the intervention group, the three questions, described above, are asked during doctor–patient consultation instead of using the DT (Table 1).

**Table 1 Tab1:** Operationalization of the outcomes and measurement points shown by outcomes

Outcome	Measure	t1	t2	t3
*Primary outcome: Psychosocial care through specialized services*				
Inpatient psycho-oncological service	Operation and procedure codes in the clinic information system or self-developed questionnaire			x
Cancer Counseling Center	Self-developed questionnaire			x
Inpatient social service	Operation and procedure codes in the clinic information system or self-developed questionnaire			x
Outpatient psychotherapy	Self-developed questionnaire			x
Neuropsychology	Medical records or operation and procedure codes in the clinic information system			x
Rehabilitation	Self-developed questionnaire or data derived from medical records			x
*Secondary outcomes*				
Percentage of patients that can be assessed for psychosocial distress	Participation rate in intervention arm vs control arm		x	
Length of doctor–patient consultation	In minutes (documentation by clinicians in the study worksheet)		x	
Emotional functioning/distress	EORTC QLQ-C30, emotional functioning scale	x		x
Health-related quality of life	EORTC QLQ-C30, global scale and BN20, all scales	x		x
Support requested	Self-developed questionnaire	x	x	x
Appointments arranged in specialized services	Documentation by clinicians in the study worksheet		x	

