Direct costs of support	Calculated on the basis of the patient–doctor consultation duration			x
Accuracy of the screening method	Comparison of the screening results regarding unmet needs (intervention vs control arm) with a detailed diagnosis based on SCID interview		x	
*Evaluation of protocol adherence*	Questions to patients: whether they have completed a DT (control arm) or whether the doctor has inquired about their psychosocial condition (intervention arm)		x	

*Abbreviations*: *EORTC QLQ-C30* European Organization of Research and Treatment of Cancer Quality of Life Core Questionnaire, BN20: brain-cancer-specific module, *SCID* Structured Clinical Interview for DSM, *DT* Distress Thermometer

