#### After the doctor–patient consultation, t2

After the doctor–patient consultation, the patients complete the above mentioned questionnaire for support needs a second time.

In addition, the Structured Clinical Interview (SCID) for DSM (Diagnostic and Statistical Manual of Mental Disorders) is conducted with the patients. The SCID is used to identify mental health conditions [20]. The interviewer asks certain questions and codes the answers in order to be able to make a diagnosis at the end. The SCID is widespread, reliable, and valid [20]. The study nurses have been trained beforehand to conduct the interviews. Each controversial case will be discussed in a telephone conference with a supervisor (Table 1).

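### Two secondary outcomes in Table 1 are paired with measures that do not capture them: accuracy for unmet needs is judged by a psychiatric interview, and support costs come from consultation time

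*Protocol article*

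**What the plan says.** The second aim, under Objectives and hypothesis, is stated as "we compare the percentage of HGG patients correctly identified as distressed in the two trial arms". Table 1 operationalizes the matching outcome, accuracy of the screening method, as "Comparison of the screening results regarding unmet needs (intervention vs control arm) with a detailed diagnosis based on SCID interview", marked at t2. The section on the t2 assessments says of the reference instrument: "The SCID is used to identify mental health conditions".

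The screens are wider than that. Besides mood, the intervention arm asks "Do physical changes due to the disease, such as numbness, weakness, or feeling exhausted more quickly, put a strain on you" and "Has your mental capacity worsened as a result of the disease, making it harder for you to concentrate or remember things, for example". The control arm's DT combines a distress rating with a "40-item list with problems from different areas of life, e.g., practical, family, emotional problems, etc". The Background counts socio-legal, rehabilitation and palliative support among what these patients need, alongside psychological support.

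Two further Table 1 rows matter. Direct costs of support, marked at t3, are "Calculated on the basis of the patient–doctor consultation duration". The share of patients who can be assessed for distress, marked at t2, is measured as "Participation rate in intervention arm vs control arm".

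**The concern.** The accuracy row names one target (unmet needs) and a reference standard for another (mental disorder). A patient with a real rehabilitation or socio-legal need and no DSM disorder is SCID-negative. If the screen counts as positive because it found that need, the comparison records a false positive for a correct detection. The two screens carry different amounts and kinds of non-psychiatric content, so the artefact need not cancel between arms. The second aim, and the abstract's secondary endpoint on distress and unmet needs detected correctly, would rest on this comparison.

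The cost row has a simpler fault. The trial is meant to increase the number of distressed patients who receive support, yet the measure for the cost of support contains no support. Consultation length is already a separate Table 1 outcome at t2, so the cost row adds little to it.

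**Working it through.** **1. The plan's own figure.** The only design figure is the total of 616. The unpooled two-proportion formula gives (1.960 + 0.842)² × (0.15×0.85 + 0.25×0.75) / 0.10² = 247.24 per arm. The design effect is 1 + (50 − 1)×0.005 = 1.245. The total is 2 × 247.24 × 1.245 = 615.6, so 616 reproduces. Nothing below depends on it or changes it.

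**2. Outcome against measure.**

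| Table 1 outcome | Stated measure | What the measure captures | What it leaves out |
|---|---|---|---|
| Accuracy regarding unmet needs | SCID diagnosis | Mental disorder | Physical, cognitive, practical, family and socio-legal needs without a disorder |
| Direct costs of support | Consultation duration | Doctor's time at the visit | All services received by t3 |

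**3. How a flawless needs screen would score against the SCID.** The documents give no prevalences, so all inputs are assumptions: unmet need n = 0.40–0.60, SCID disorder d = 0.15–0.30, and share of patients with a disorder who also have a need c = 0.70–1.00. If the screen is positive exactly when a need exists:

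- Sensitivity = c = 0.70 to 1.00.
- Specificity = 1 − (n − dc)/(1 − d). Lowest (n = 0.60, d = 0.15, c = 0.70): 1 − (0.60 − 0.105)/0.85 = 0.42. Highest (n = 0.40, d = 0.30, c = 1.00): 1 − 0.10/0.70 = 0.86.
- Positive predictive value = dc/n, from 0.105/0.60 = 0.175 to 0.30/0.40 = 0.75.

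The screen makes no error about needs, so every apparent error comes from the choice of reference.

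**4. How the metric can decide the comparison.** Assume 30% are SCID-positive. The three questions flag 80% of patients with sensitivity 95%, and the DT flags 50% with sensitivity 75%. All five inputs are assumptions.

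| | Three questions | DT |
|---|---|---|
| True positives, all patients | 0.30×0.95 = 28.5% | 0.30×0.75 = 22.5% |
| False positives | 80 − 28.5 = 51.5% | 50 − 22.5 = 27.5% |
| True negatives | 70 − 51.5 = 18.5% | 70 − 27.5 = 42.5% |
| Specificity | 18.5/70 = 26% | 42.5/70 = 61% |
| Overall correct | 28.5 + 18.5 = 47% | 22.5 + 42.5 = 65% |

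The intervention looks better on true positives and the control looks better on the other two. This depends on the flag rate. Let the questions flag a share f and hold the other inputs fixed. Their specificity is lower than the DT's only if f − 0.285 > 0.275, that is f > 0.56. Overall correct classification, 2×0.285 + 0.70 − f = 1.27 − f, is below 0.65 only if f > 0.62. Below f = 0.56 the intervention is ahead on all three.

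**5. Costs.** If cost is a function of consultation minutes alone, two arms with equal consultation times have equal cost, whether 15% or 25% of distressed patients (the planning assumptions) receive care. The expected 10-point difference contributes nothing.

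**The case against.** The strongest defence is that the second aim speaks of distress, and the SCID is a legitimate if partial reference for mental distress. That stands: the fault lies in the words about unmet needs, not in using the SCID. It would be too strong to infer that the second aim cannot be addressed.

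The article gives no rule by which one yes among the three questions makes a positive screen; the doctor offers care if it is indicated and the patient wants it. The scoring error is therefore conditional on how positivity is defined. The DT problem list has the same mismatch, so the documents do not support reading this as an error in the intervention arm only, or as one that favours the control. Table 1 also fixes no accuracy metric. Leaving that to an analysis plan is normal and not a fault.

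A reader might infer that assessability is measured by consent to the trial and so is never observed. The article does use participation for joining the study. But this row is marked at t2, after the consultation, and can mean taking part in the screening. At t2 patients are also asked whether they completed a DT or whether the doctor inquired about their psychosocial condition. The wording is ambiguous, which calls for clarification and nothing more.

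Finally, the article does not rank its secondary outcomes, and the section on primary and secondary endpoints lists neither costs nor assessability, so these rows should not be called key outcomes. The article's brevity does not excuse the two mismatches, because Table 1 expressly states the measures.

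**Conclusion.** The point holds for two rows of Table 1. Accuracy regarding unmet needs cannot be established against a SCID diagnosis. Where a screen is positive on a non-psychiatric need, correct detections without a disorder are counted as errors, possibly to different degrees in the two arms. Direct costs of support, computed from consultation duration, cannot reflect support received.

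The size is not known from the documents. The apparent specificity of 0.42–0.86 for a flawless needs screen holds only over the assumed ranges. The two-arm illustration shows only that the choice of metric can decide which arm looks better; it does not predict either direction. The participation-rate row is a minor matter of wording. The primary endpoint and the total of 616 are unaffected.

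**What to change.** 1. **Accuracy.** Restate the Table 1 outcome as accuracy for mental disorder. Compare the mood question (intervention) and the DT distress score (control) with the SCID, and report sensitivity and specificity separately by arm. Make no claim about unmet needs from the SCID. At most, describe agreement of the full screen with the support-requested questionnaire as a secondary result. Note there that the form is self-completed, in a population chosen partly because forms are hard for them, and that it records wish for support rather than need.
2. **Costs.** Rename the item consultation time cost. Cost the services recorded at t3 only if quantities are available: Table 1 lists which services were received, not the number of contacts, and the article shows no recording of DT administration time.
3. **Clarification.** State that participation rate means completion of the assigned screen among enrolled patients, not consent to the study. The t2 adherence item offers a patient-reported source; the article does not say that the worksheet records completion.

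Items 1 and 3 and the renaming are changes of wording that use planned data. The price is a narrower accuracy claim and two figures instead of one. Costing the services could need data that the article does not show being collected.

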#### After the doctor–patient consultation, t2

After the doctor–patient consultation, the patients complete the above mentioned questionnaire for support needs a second time.

In addition, the Structured Clinical Interview (SCID) for DSM (Diagnostic and Statistical Manual of Mental Disorders) is conducted with the patients. The SCID is used to identify mental health conditions [20]. The interviewer asks certain questions and codes the answers in order to be able to make a diagnosis at the end. The SCID is widespread, reliable, and valid [20]. The study nurses have been trained beforehand to conduct the interviews. Each controversial case will be discussed in a telephone conference with a supervisor (Table 1).

#### Follow-up, t3

Three months later, the patients will complete the EORTC QLQ-C30 + BN20 questionnaire and again an adapted version of the self-developed questionnaire (Table 1) in order to assess the proportion of patients receiving adequate care.

#### Training of study personnel and monitoring

During the start-up phase of the study, the research assistants and study nurses have been trained to conduct the SCID interview reliably. They also learned about the assessment procedures at t1–t3. Furthermore, worksheets and case report forms (CRFs) have been developed, evaluated, and adapted after a pilot test in September 2019. All centers will be initiated and monitored by the project manager of the study. Frequently (monthly) conducted telephone conferences regarding the SCID interview and study meetings planned twice a year will help to solve any problems.

### Statistics

#### General considerations for data analysis and statistical methods of the study

Through cluster randomization, the study can be better implemented into clinical routine.

Broadly selected inclusion criteria ensure that as many patients as possible are reached. The aim is to include not only highly selected patients.

#### Data management

Data will be derived from patients’ responses to questionnaires, worksheets completed by study nurses and research assistants, as well as from medical records. All data will be collected specifically for research purposes.

All person-identifying data are avoided in the data set and code numbers used instead. A study code will be assigned to each subject in the respective study center. A copy of all worksheets and completed questionnaires using the code numbers will be sent to the statistical center (IMBEI) in Mainz. Only pseudonymized data will be handed over. All study data will be stored for 10 years after completion of the study in the respective center, and only the study team will have access to the data. In Mainz the central data processing and evaluation will be done. Pseudonymized data will be stored in a password-protected electronic database, which is stored in a locked server only accessible for staff members of the IMBEI with access authorization.

#### Sample size

Based on previous studies [21] we expect that in the control group only about 15% of mentally stressed patients receive psychosocial care compared to an expected 25% in the intervention group.

Due to the fact that this is a cluster-randomized study, more patients have to be included in the study.

The sample size calculation is based on recommendations by Hayes and Bennett, who developed several scenarios for cluster-randomized studies and provided formulas for the calculation of the cluster effect. The intracluster correlation coefficient (ICC) in a comparable, cluster-randomized study with 13 clusters was between 0.03 and 0.19 depending on the outcome [21]. However, Donner and Klar (2004) warn of overestimating the stability and size of an ICC. Therefore, we assume an ICC of 0.005. We further assume that 50 patients will be included in the study in each clinic and that the clusters will be of the same size. In this scenario (ICC 0.005), 12 clinics with a total of *n* = 616 patients are required to demonstrate the expected intervention effect (25% vs 15%) with α of 0.05 and a power of 80%.

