**Methods/design:**

This is a multicenter cluster randomized study with two arms. Randomization is done on a cluster level with 13 hospitals providing regular neuro-oncological outpatient services conducted by neurologists and/or neurosurgeons. The intervention will include an assessment of psychosocial distress of patients in doctor–patient conversation compared to assessment of psychosocial distress via questionnaire (control, standard of care).

In total, 616 HGG patients will be enrolled. The outcome will be the number of HGG patients with increased psychosocial distress who receive professional support from psychosocial services.

Secondary endpoints are inter alia number of patients reporting psychosocial distress and unmet needs detected correctly by the respective method; quality of life; psychological well-being and burden of the patients before and after doctor–patient consultation; as well as the length of the doctor–patient consultation.

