### Primary and secondary endpoints

The primary endpoint is the proportion of patients with increased psychosocial stress who receive professional support from psychosocial services (psycho-oncology, social services, cancer counseling centers, palliative care with psychosocial support).

Secondary endpoints are number of patients reporting psychosocial stress; number of patients receiving psychosocial care through specialized services such as psycho-oncology, social services, cancer counseling centers, palliative care, etc.; number of patients referred to care structures; quality of life; need for support; psychological well-being and burden of the patients before and after doctor–patient consultation; and duration of the doctor–patient consultation.

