### Participants and procedures

#### Eligibility criteria

Clusters: Departments as clusters were included, when 1) a neuro-oncological outpatient service was present with 2) regular weekly consultation hours and 3) conducted by neurologists or neurosurgeons.Patients: We include patients with a HGG (glioblastoma WHO°IV, anaplastic astrocytoma WHO°III, anaplastic oligodendroglioma WHO°III) aged 18 years and older with the ability to give informed consent. Patient exclusion criteria are absence of written informed consent and inability to understand the German language.

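### The 616 patients are sized as if all were distressed, but any high-grade glioma patient can enter and only distressed patients count in the primary analysis, so the stated 80% power is not delivered

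*Protocol article*

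**What the plan says.** In the protocol article, Sample size, the planning rates are conditional on distress: "we expect that in the control group only about 15% of mentally stressed patients receive psychosocial care compared to an expected 25" per cent. The total is then justified by those rates: "patients are required to demonstrate the expected intervention effect (25% vs 15%) with α of 0.05 and a power of 80" per cent. The clustering inputs are also given there: "Therefore, we assume an ICC of 0.005", and "We further assume that 50 patients will be included in the study in each clinic and that the clusters will be of the same size". Clustering is the only reason given for raising the number of patients.

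The section Primary and secondary endpoints uses the same restricted denominator: "The primary endpoint is the proportion of patients with increased psychosocial stress who receive professional support from psychosocial services". Objectives and hypothesis (the PICO outcome) and Statistical analysis agree with it.

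The abstract applies the number to everyone who enters: "In total, 616 HGG patients will be enrolled". Under Eligibility criteria, a patient needs a high-grade glioma and must be "aged 18 years and older with the ability to give informed consent". The exclusions are lack of consent and inability to understand German, and no level of distress is required. Table 1 and the section Follow-up, t3 place the primary outcome three months after the consultation.

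**The concern.** A sample size computed from rates among distressed patients is a number of distressed patients with a known outcome. Here it is used as the number of patients enrolled, whatever their distress. The protocol itself expects some of them not to be distressed. The number reporting distress is a secondary endpoint, and the second aim compares how often distress is correctly identified. Neither would make sense if all 616 were distressed by design.

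The primary denominator is therefore 616 × (share distressed) × (share with a three-month outcome). If it is well short of 616, a true 10-point effect is more likely to be missed than planned, and a null result would be read as coming from an 80%-powered trial.

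**Working it through.** **Inputs from the article:** rates 15% and 25%; α 0.05; power 80%; ICC 0.005; 50 patients per clinic; 12 clinics in the calculation and 13 taking part; 616 in total. Sidedness and formula are not stated. A two-sided test reproduces 616; a one-sided test gives about 490 and does not.

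**Step 1: reproduce 616.**
- Per arm without clustering: (1.960 + 0.842)² × (0.15 × 0.85 + 0.25 × 0.75) / 0.10² = 247.24.
- Design effect: 1 + (50 − 1) × 0.005 = 1.245.
- Total: 2 × 247.24 × 1.245 = 615.6, rounded up to 616.

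The two rates, α, power and clustering use up the whole figure. No factor is left for prevalence of distress or for attrition.

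**Step 2: power at the number analysed.** Neither the distressed share nor a loss rate is in the article, so both are assumptions. For N analysed patients in 13 clinics with equal arms:
- m = N/13, and design effect DE = 1 + (m − 1) × 0.005
- effective number per arm = (N/2)/DE
- power = Φ(0.10/SE − 1.960), with SE = √(0.315 / effective number), where 0.315 = 0.1275 + 0.1875

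Worked case, 50% distressed and no loss: N = 308; m = 23.7; DE = 1.1135; effective number = 154/1.1135 = 138.3; SE = √(0.315/138.3) = 0.0477; 0.10/0.0477 − 1.960 = 0.135; power = 55%.

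| Assumed share distressed | N, no loss | Power | N, 20% lost | Power |
|---|---|---|---|---|
| 100% | 616 | 80% | 493 | 73% |
| 90% | 554 | 77% | 443 | 69% |
| 80% | 493 | 73% | 394 | 65% |
| 70% | 431 | 68% | 345 | 60% |
| 50% | 308 | 55% | 246 | 47% |
| 30% | 185 | 38% | 148 | 32% |

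The lower design effect of smaller analysed clusters is already included and only partly offsets the loss of patients. Using 12 clinics, a pooled variance or a 6-to-7 split of clinics moves these figures by about one point.

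**Step 3: detectable difference at 50% distressed, no loss.** With 138.3 effective patients per arm, try 15% versus 28.7%: SE = √((0.1275 + 0.287 × 0.713)/138.3) = 0.0490, and 2.802 × 0.0490 = 0.137, which equals the difference. The detectable contrast is about 15% versus 29%.

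**Step 4: enrolment that would yield 616 distressed patients, no loss.** 616/0.8 = 770; 616/0.7 = 880; 616/0.5 = 1,232; 616/0.3 = 2,054 (rounded up).

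**The case against.** The strongest reply concerns size. The article gives no prevalence of distress, and it describes this population as often highly distressed. At shares of 80–90% with no loss, power is still 73–77%. That is a fair caution, and the table includes those rows. It does not rescue the 80% claim, which needs a share of about 100%.

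The attrition part is softer. Table 1 lets four of the six components of the primary outcome come from procedure codes or medical records (inpatient psycho-oncology, inpatient social service, neuropsychology, rehabilitation), so a missing three-month questionnaire is not always a missing outcome. The 20% loss is purely illustrative. Intent to treat is specified, but it does not by itself supply missing outcomes. This part is therefore secondary, and the distress restriction carries the point alone.

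The wording of the outcome also varies: the Table 1 label carries no distress restriction, and the abstract speaks of a number rather than a proportion. The objectives, the endpoint section and the analysis section all restrict it to distressed patients. If all enrolled patients were meant instead, rates of 15% and 25% among the distressed would be the wrong planning rates.

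Finally, every figure holds the ICC at 0.005. The same section cites 0.03 to 0.19 from a comparable trial. At 0.03 with 12 clinics, power is about 50% even with all 616 analysed. The figures above are thus conditional on the protocol's own ICC and are not estimates of the trial's actual power.

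**Conclusion.** The concern holds. As written, 616 enrolled patients do not give 80% power for 25% versus 15% among distressed patients, because 616 is the number of distressed patients required. The direction follows from the article alone. The size depends on two quantities it does not give. At ICC 0.005 with 13 clinics and no loss, power runs from about 73% (80% distressed) through 55% (50%) to 38% (30%). With an assumed 20% loss as well, these become 65%, 47% and 32%. Because this is the headline power statement for the primary endpoint, it must be corrected.

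**What to change.** Keep enrolment at 616 and replace the power sentence in Sample size. The new text should give:

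- the expected share of enrolled patients meeting the trial's definition of increased distress, as a range with its source;
- the expected share of those with a primary outcome at three months, allowing for what can be recovered from records;
- the resulting number analysed, with cluster size counted in those patients;
- the power for 25% versus 15%, or the difference detectable with 80% power, at that number.

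The text should no longer say that 616 enrolled patients give 80% power. The article reports the study as ongoing, so distress and follow-up counts pooled over both arms could supply the two shares without comparing the arms.

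The cost is a rewritten paragraph and a less favourable power figure, with no extra patients. This corrects the claim but does not restore the power. Restoring it would mean the larger enrolments in step 4 of the working, for example 1,232 at 50% distressed, which is double the plan.

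### The sample size assumes an ICC of 0.005, below the whole range the plan cites (0.03 to 0.19), so the stated 80% power holds only at an unsupported value

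*Protocol article*

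**What the plan says.** All of this stands in the protocol article, Statistics, Sample size.

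- Expected rates: "in the control group only about 15% of mentally stressed patients receive psychosocial care", "compared to an expected 25% in the intervention group".
- Error rates: "with α of 0.05 and a power of 80" percent. Sidedness is not stated.
- Empirical clustering: "The intracluster correlation coefficient (ICC) in a comparable, cluster-randomized study with 13 clusters was between 0.03 and 0.19 depending on the outcome". The same reference is cited for the expected rates of care.
- Reason for departing from that range: a methods source is said to "warn of overestimating the stability and size of an ICC".
- Choice made: "Therefore, we assume an ICC of 0.005".
- Cluster size: "We further assume that 50 patients will be included in the study in each clinic and that the clusters will be of the same size".
- Result: 12 clinics and 616 patients. The abstract and the Setting section give 13 clinics for the trial itself.

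The Statistical analysis section plans a hierarchical model with a random intercept for clinic, adjusted for seven patient variables.

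**The concern.** The only empirical ICCs in the document lie between 0.03 and 0.19, and the planning value lies below all of them: 0.03 / 0.005 = 6 and 0.19 / 0.005 = 38. With about 50 patients per clinic, the design effect depends strongly on the ICC, so this one choice largely determines whether 616 patients are enough.

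The endpoint also gives reason to expect clustering. It is receipt of psychosocial services. The section on psychosocial care in both arms ties the timing of care to the capacity of the local cooperating services. The section on bias and confounding lists hospital organization, individual doctors, local conditions and resources as influences. Randomizing 13 hospitals aims to balance such factors between arms, but it does not remove the between-hospital variation that makes up the ICC.

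At stake is how the result is read. If clustering is stronger than assumed, a real difference of 15% vs 25% could easily be missed, and the null result could then be taken as evidence from a trial with 80% power.

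**Working it through.** **Inputs.** From the Sample size section: p1 = 0.15, p2 = 0.25, alpha 0.05, power 80%, m = 50 per clinic, ICC 0.005 assumed, 0.03 to 0.19 cited. Assumed because not stated: two-sided test and 1:1 allocation. The reproduction below supports both.

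**Step 1: reproduce 616.**

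- Variance term: 0.15 × 0.85 + 0.25 × 0.75 = 0.1275 + 0.1875 = 0.315.
- Per arm without clustering (unpooled): (1.960 + 0.842)² × 0.315 / 0.10² = 7.849 × 31.5 = 247.24.
- Design effect: 1 + (50 − 1) × 0.005 = 1.245.
- Total: 2 × 247.24 × 1.245 = 615.6, rounded up to 616.

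The plan's figure is reproduced. Since 616 / 50 = 12.3, it is slightly more than 12 clinics of 50 (600).

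**Step 2: total needed for 80% power at the cited ICCs, m = 50.**

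- ICC 0.03: design effect 1 + 49 × 0.03 = 2.47; 2 × 247.24 × 2.47 = 1,221 patients, about 25 clinics.
- ICC 0.19: design effect 1 + 49 × 0.19 = 10.31; 2 × 247.24 × 10.31 = 5,098 patients, about 102 clinics.

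**Step 3: power with 616 patients.** Effective size per arm is n_eff = 308 / DE, and power = Φ(0.10 / √(0.315 / n_eff) − 1.960). Worked example for 13 clinics (m = 616 / 13 = 47.4) and ICC 0.03: DE = 1 + 46.4 × 0.03 = 2.39; n_eff = 308 / 2.39 = 128.8; standard error = √(0.315 / 128.8) = 0.0495; 0.10 / 0.0495 = 2.02; power = Φ(0.06) = 0.525.

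The ranges below cover 12 clinics (m = 51.3) and 13 clinics (m = 47.4), with pooled or unpooled variance.

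| ICC | DE, 13 clinics | n_eff per arm, 13 clinics | Power, 12 to 13 clinics |
|---|---|---|---|
| 0.005 | 1.23 | 250.0 | 79-80% |
| 0.01 | 1.46 | 210.4 | 72-73% |
| 0.02 | 1.93 | 159.8 | 59-62% |
| 0.03 | 2.39 | 128.8 | 50-53% |
| 0.19 | 9.81 | 31.4 | 16-17% |

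**Step 4: small number of clusters.** Replacing the normal reference by a t reference on 10 to 11 degrees of freedom (clinics minus 2) gives about 71-73% at 0.005, 43-46% at 0.03 and 14-15% at 0.19.

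**Step 5: detectable difference at ICC 0.03, 13 clinics.** Solve (p2 − 0.15) / √((0.1275 + p2(1 − p2)) / 128.8) = 2.802. This gives p2 = 0.293, so about 15% vs 29%.

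**Step 6: can more patients per clinic repair it?** As m grows without limit, n_eff per arm tends to (clinics / 2) / ICC. At ICC 0.03 that is 6 / 0.03 = 200 for 12 clinics and 6.5 / 0.03 = 217 for 13, with power of about 71-75%. Longer recruitment in the same clinics would not reach 80%.

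**The case against.** Four points can be made for the plan.

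*The stated reason concerns size as well as stability.* A warning against overestimating the size of an ICC does point downwards, so it would be unfair to treat the rationale as an appeal to instability alone. This stands. But the document takes no number from the warning, and a general caution does not carry the assumption below every value cited.

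*The cited range may not apply to this endpoint.* It varied by outcome, came from only 13 clusters and is therefore imprecise. The document does not say which value, if any, belongs to receipt of psychosocial care. Adjustment for patient variables could also lower the residual ICC by an unknown amount. This stands too. A reader might infer that the trial's actual power is 53% or less, but the document does not support that as a fact: it follows only if the true ICC is at least 0.03. Intermediate values give intermediate losses.

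*The analysis allows for clustering.* The random intercept for clinic estimates the clustering that is actually present. So one should not infer that the optimistic ICC by itself biases the effect estimate or inflates the type I error. The harm is to power and to the reading of a null result.

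*The full protocol may contain other scenarios.* The article refers to the ICC of 0.005 as one scenario, and a power table could well sit elsewhere. That would not repair the reasoning and the power claim printed here.

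**Conclusion.** The point holds in a conditional form. The ICC of 0.005 has no quantitative support in the document and lies six times below the lowest value cited. The 80% power is correct arithmetic at 0.005 and is not robust to that choice: about 72-73% at 0.01, 50-53% at 0.03 and 16-17% at 0.19, and lower still with a t reference.

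These figures rest on a two-sided test, 1:1 allocation, equal clusters, and all 616 patients entering the primary analysis. The last assumption is generous, because the 15% and 25% rates refer to distressed patients only.

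A reader might also conclude that 0.03 should simply be named the planning value. With 616 patients and 13 clinics kept, that would describe a trial planned at about 50-53% power, for an N that was derived at 0.005. The documents do not establish 0.03 for this endpoint either. An open range is the sounder statement.

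**What to change.** In the Sample size section:

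1. Remove the step from the general warning to 0.005 as support for 80% power, and say that 80% applies only if the ICC is 0.005.
2. State power and detectable difference for the fixed 13 clinics and 616 patients over ICC 0.005 to 0.19. At 0.03 this is about 50-53% power and a detectable difference of about 15% vs 29%.
3. Commit to reporting the observed ICC of the primary outcome with its confidence interval.
4. Commit to interpreting a non-significant result through the confidence interval of the effect, and not as evidence of no effect from a trial with 80% power.

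The cost is a rewording and a less favourable stated power. No patients or clinics are added, and the planned model does not change. The rewording does not raise the power of the trial; it makes the stated power honest.
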